#### *Cost-effectiveness*

We will perform a cost-utility analysis alongside the trial from a societal perspective with a time horizon of one year comparing active cTBS to sham cTBS. In a scenario analysis, we will show the impact on cost-effectiveness, if effects at one year would be extrapolated over time. Sham stimulation could have a placebo effect; however, the magnitude of the placebo effect is unsure. A scenario analysis will be performed to show the potential impact of the placebo effect on cost-effectiveness results.

Quality of life will be assessed by combining mortality and quality of life using an area-under-the-curve approach. Quality of life will be assessed with the EQ-5D-5L. The Dutch tariffs will be used to calculate answer into a utility score. This utility score can range up to 1, in which 0 corresponds to death and 1 corresponds to perfect health.

Costs of the interventional procedures itself will be calculated with a bottom-up approach or estimated based on financial information from the rehabilitation centers. In a scenario analysis, we will estimate cost-effectiveness if we exclude navigation costs during the procedure.

Other healthcare resource use will be assessed in two ways. Direct healthcare costs during clinical rehabilitation will be estimated for each center based on the length of stay (LOS) of a patient. LOS will be calculated based on the date of admission and the date of discharge at the rehabilitation center. These dates will be requested from the administrative department of each rehabilitation center. Healthcare costs after clinical rehabilitation will be collected through CASTOR at 6 and 12 months post-stroke using an adaptation of the iMTA Medical Consumption Questionnaire (iMCQ). Data will be extrapolated to fill in missing data caused by the recall-period of three months. The iMCQ will be used to measure all direct medical costs (consultations, hospitalizations), and direct non-medical costs (family care). Healthcare resource use will be multiplied with Dutch unit costs to determine healthcare costs. Unit costs will be used as described in the Dutch Costing guideline; NZA tariffs or internal UMCU tariffs if both are missing.

The Productivity Cost Questionnaire (iPCQ) will be sent out through CASTOR at 6 and 12 months post-stroke to collect productivity losses for each individual patient. The iPCQ will consist of two modules: lost productivity at paid work due to absenteeism and lost productivity at paid work due to presenteeism. Data will be extrapolated to fill in missing data caused by the recall period of four weeks.

Missing data will be imputed with multiple imputation and the uncertainty of the economic evaluation will be assessed with bootstrapping techniques.

To be able to extrapolate trial findings and to perform other scenario analysis; a decision-analytical model (a decision tree) will be developed. In this decision tree, we will correlate trial findings in EQ-5D-5L and costs to outcomes in Fugl-Meyer.

A detailed protocol for the cost-effectiveness study will be prepared separately.

### **8.1.3 Other study parameters (if applicable)**

#### **Baseline values**

##### *Demographic information*

Sex, age, education level based on the international standard classification of education (ISCED), handedness, marital status, work status, ethnicity.

##### *Medical history*

Diabetes mellitus, hypertension, smoking

##### *Medication*

Current medication

##### *Stroke parameters*

Type of stroke, stroke location (including affected hemisphere or brain stem), National Institutes of Health Stroke Scale (NIHSS) at admission to the hospital, date of stroke onset, treatment with intravenous thrombolysis or endovascular thrombectomy in the acute phase, Montreal Cognitive Assessment (MOCA) at admission to rehabilitation center, O-letter cancellation test, pre-stroke score on the mRS.

##### *Baseline neurological and functional status*

FM-UE, ARAT, NHPT, mRS, SIS, BI, EQ-5D-5L, ability to extend 1 or more fingers of the paretic arm, motricity index,

##### *Baseline electrophysiology*

Corticospinal excitability

## 8.2 Randomization, blinding and treatment allocation

Patients will be randomly allocated to receive active or sham continuous theta burst stimulation (cTBS) treatment. Randomization will be executed through a web-based allocation service (CASTOR) that generates a unique study number for each participant. Randomization is stratified based on the ability to extend one or more fingers of the paretic arm and the rehabilitation center at which the participant is recruited. Information on treatment allocation will be kept separate from the main study database. Patients will be randomly allocated to group A or group B, to allow double-blinding.

Sham cTBS will be performed using a sham TMS coil, which looks identical to an active TMS coil but does not produce effective stimulation. The sham and active TMS coils will be labeled with a code (A/B) by the coordinating investigator who is not involved in any of the TMS treatments. The TMS therapist performs randomization and patients will be allocated to receive treatment with coil A or B, depending on their group allocation (A/B). Therefore, the TMS therapists and patients are unaware of treatment allocation. Blinding of the patient and therapist will be maintained until the last patient has completed the final follow-up (at 12 months post-stroke). Only one of the coordinating investigators can link treatment allocation to the active or sham condition. The independent trial statistician will combine data on treatment allocation with the clinical data to report to the data safety monitoring board (DSMB). The treatment allocation code will not be broken until the database has been locked, which is after the all data have been cleaned. The moment of datalock is defined in the statistical analysis plan. Cleaning of the data will be performed by a coordinating investigator who is unaware of treatment allocation.

## 8.3 Study procedures

A local investigator will perform screening and the informed consent procedure described in section 11.1. After written informed consent is obtained, baseline assessments will be performed. Baseline assessment duration is up to 90 minutes. Descriptions of the study procedures to determine the outcome measures (Table 1) are provided below.

After the baseline assessments, patients undergo the intervention described in section 5.1. The following data related to cTBS treatment is acquired: date and time of each treatment, the resting motor threshold, experienced side-effects and the number of minutes of upper limb therapy after the previous session. At the end of treatment course, the following data is acquired: the number of completed treatments,

the duration of the treatment course in days, and whether the patient thinks he/she received active or sham treatment.

At 90 days and 12 months post-stroke, the outcome measures described in table 1 are reassessed. Follow-up assessment duration is up to 90 minutes per follow-up. Detailed descriptions of these tests are provided below.

After the patient has been discharged, the total amount of upper limb therapy received during clinical rehabilitation and the length of stay at the rehabilitation center are acquired.

### **Upper extremity section of the Fugl-Meyer assessment (FM-UE)**

The upper extremity section of the Fugl-Meyer assessment is a reliable and valid motor performance test consisting of 33 tasks performed with the affected upper limb. The FM-UE evaluates the ability to make movements outside the synergistic pattern. Performance on each task is rated as 0, 1 or 2, with a maximum score of 66 points and with a higher score indicating less impairment.

### **Action research arm test (ARAT)**

The ARAT is an upper limb performance test which assesses the ability to perform gross movements and the ability to grasp, move and release objects differing in size, weight and shape. The test consists of 19 items, rated on 4-point ordinal scales (0 to 3), with a maximum score of 57. A higher score indicates better performance.

### **Nine Hole Peg Test (NHPT)**

The NHPT examines fine motor skills and manual dexterity. The patient must put 9 pegs into slots and individually place them back into a bin as quickly as possible with the affected hand. The test's outcome is the execution duration, with a maximum duration of 50 seconds, and the number of pegs that have been moved (within the 50 second time window), with a maximum of 18 points (1 point per peg movement). Reliability and validity have been demonstrated in stroke patients.

### **Modified Rankin Scale (mRS)**

The modified Rankin Scale measures the degree of disability and dependence on an ordinal scale from 0 (no symptoms) to 5 (severe disability) and 6 (death).

### **O-letter cancellation test (OCT), only at baseline**

The O-letter cancellation test is a screening tool for unilateral spatial neglect. In the OCT there are 40 O-letters interspersed with other letters shown on a piece of paper. The patient must cross out all the O-letters. The time to complete the test and the number of correctly crossed out O-letters on the contralateral and ipsilesional side are recorded.

### **Stroke Impact Scale**

The Stroke Impact Scale (SIS) is a self-report questionnaire for the evaluation of disability and health-related quality of life after stroke. Three sections that are directly or indirectly related to upper limb recovery will be assessed: hand function, participation and overall recovery.

### **Barthel index**

The BI is an ordinal scale used to measure performance in 10 activities of daily living. Test scores range from 0 to 100, with higher scores indicating better performance in these activities

### **EuroQol-5D-5L**

The EuroQol-5D-5L is a quality-of-life questionnaire. It consists of 5 questions with 5 answer possibilities each. Each question captures one dimension of quality of life: mobility, self-care, daily activities, pain or other complaints, and anxiety/depression.

### **Contralesional corticospinal excitability**

Corticospinal excitability is determined based on the RMT (defined under section 5.1). The contralesional RMT is assessed before the 1st, 6th and 10th cTBS session, as part of the treatment procedure described under section 5.1. Therefore, it does not require additional measurements.

### **Ipsilesional corticospinal excitability (optional)**

Ipsilesional excitability (i.e. the RMT) is assessed at baseline and directly after 10 cTBS sessions.

### **Contralesional inhibition (optional)**

Contralesional inhibition is determined based on the ratio between the average MEP amplitude in response to 10 stimuli at 110% RMT before and after cTBS sessions 1, 6, and 10. The stimulation location is the motor hotspot, as identified prior to cTBS

treatment (to determine the cTBS treatment location). The RMT is also determined before the 1st, 6th and 10th cTBS treatment (to determine cTBS stimulation intensity).

TMS disruption (optional)

TMS disruption consists of a train of 30 active or sham TMS pulses at 10Hz and 90% RMT, delivered over the contralesional M1. The participant is instructed to start tapping the index finger of the affected hand at the onset of an auditory stimulus at 0s for a duration of 3 seconds at maximum frequency. The train of TMS pulses covers the entire finger tapping period. Finger tapping frequency is recorded using a key on a keyboard with the wrist fixed to the table using a velcro strap to minimize variability in task execution. 5 sessions of sham and 5 sessions of active TMS interference of the contralesional M1 are acquired.

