## 6. INVESTIGATIONAL PRODUCT

### 6.1 Name and description of investigational product(s)

CTBS treatment will be delivered using a therapeutic biphasic magnetic stimulator that supports the continuous theta burst stimulation protocol described in section 5.1 with a pulse width between 250 and 330 microseconds, includes cooling and an integrated one- or multi-channel electromyography (EMG) system and three separate figure-of-eight TMS coils for motor-threshold determination, active and sham stimulation. Currently, the following three CE-certified TMS devices with an intended use that covers the application described in this protocol are available:

- The MagVenture MagPro R30 stimulator with an MCF-B70 figure-of-eight TMS coil;
- The Deymed DuoMag XT-100 stimulator with a figure-of-eight TMS coil.
- The Neurosoft neuro-MSX stimulator with angulated figure-of-eight TMS coil.
- The MagStim Super Rapid stimulator with cooled Air Film Coil.
- The MagStim Horizon 3.0 with figure-of-eight TMS coil.

TMS coil placement during cTBS treatment will be guided and recorded using a compatible MRI-guided neuronavigation system that supports standard head model import. The following three compatible CE-certified neuronavigation systems with an intended use that covers the application described in this protocol are available:

- The Brain Science Tools neural navigator: Essentials and Atlas variants. Both variants will be used in combination with the headband of the Atlas variant.
- The Localite TMS navigator
- MagStim StimGuide+ (as part of the Horizon 3.0 system)

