#### **8.1.2 Secondary study parameters/endpoints**

A detailed description of secondary outcomes and assessments are provided in section 8.3.

Secondary endpoints are the FM-UE at 12 months post-stroke and the Action Research Arm Test (ARAT), nine hole peg test (NHPT), modified Rankin scale (mRS), hand and participation sections of the stroke impact scale (SIS), Barthel Index and the EuroQol - 5 dimensions – 5 levels (EQ-5D-5L) at 90 days and 12 months post-stroke.

An additional secondary outcome is the change in contralesional corticospinal excitability during the course of treatment. Therefore, the contralesional RMT is measured prior to each cTBS session (these data are already acquired to determine stimulation intensity). Contralesional inhibition is assessed to determine whether cTBS treatment had a direct inhibitory effect. This is done for cTBS session 1, 6 and 10 by acquiring the average MEP amplitude for 10 TMS pulses delivered to the contralesional M1 at 110%RMT.

Furthermore, a secondary outcome is the ipsilesional corticospinal excitability directly after the final cTBS session. Therefore, the ipsilesional RMT is measured before the first and after the final cTBS session.

TMS disruption will be assessed at baseline to determine whether contralesional M1 activity is maladaptive for affected hand performance, as this may predict cTBS treatment outcome. This will only be performed at De Hoogstraat Rehabilitation.

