## 2. Study design

B-STARS2 is a multi-centre, double-blind, randomised, sham-controlled, clinical trial.

Participants will be recruited from 16 rehabilitation centres in the Netherlands over a period of 51 months (Q2 of 2024 to Q4 of 2028). The total duration of follow-up for each participant is until one year after stroke. The total study duration is 63 months.

Baseline assessment will be performed before the start of the intervention, which must occur within 21 days after stroke onset. Follow-up assessments will be performed at 90 days (+/- 7 days) and 12 months (+/- 14 days) post-stroke (Figure 1).

The intervention consists of ten daily sessions of active or sham cTBS, delivered over the contralesional primary motor cortex, started within 21 days post-stroke and combined with regular care upper limb therapy.

Participants are randomly assigned in a 1:1 ratio to one of the two treatment groups (group A or B) using a web-based data management service. Treatment allocation is stratified by rehabilitation centre and the ability to extend one or more fingers of the affected hand.

An independent DSMB is monitoring the safety of participants of the trial. The DSMB meets at least annually. An independent statistician will perform unblinded interim analyses on all reported (serious) adverse events after 150 and 300 patients have completed the 90 days post-stroke follow-up. The independent statistician will report the outcome of the interim analyses directly to the DSMB, as well as listings of all SAE reports and unblinded aggregate summaries of data by treatment group for review in closed meetings. Feedback, blind to treatment, will be provided in written conclusions to the B-STARS2 project leaders.

[figure not shown]

**Figure 1.** Study timeline.

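### An optional baseline test at De Hoogstraat gives the same participant active and sham stimulation over the treatment target, with no stated safeguard for masking

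*Combined protocol and SAP*

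**What the plan says.** Four parts of the plan bear on this.

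- **The test.** Protocol section 8.3, under the optional TMS disruption entry: "TMS disruption consists of a train of 30 active or sham TMS pulses at 10Hz and 90% RMT, delivered over the contralesional M1". It continues: "5 sessions of sham and 5 sessions of active TMS interference of the contralesional M1 are acquired". The participant taps the index finger of the affected hand throughout each train.
- **When and where.** Protocol section 8.1.2: "TMS disruption will be assessed at baseline", because the result may predict response to cTBS, and "This will only be performed at De Hoogstraat Rehabilitation". SAP section 2: "Participants will be recruited from 16 rehabilitation centres in the Netherlands".
- **The masking.** Protocol section 8.2 labels the active and sham coils A and B and allocates participants to a coil by letter. It concludes: "Therefore, the TMS therapists and patients are unaware of treatment allocation". Only one coordinating investigator can link the letters to the conditions, and masking is to last until the final 12-month visit.
- **The equipment.** Protocol section 6.1 lists "three separate figure-of-eight TMS coils for motor-threshold determination, active and sham stimulation". Section 5.1 says that the sham coil matches the active coil in look and sound and has a much reduced field. It does not mention sensation on the scalp.

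**The concern.** The primary objective is a comparison with sham, so it depends on participants and therapists not knowing which coil is in use. The disruption test lets a participant experience both conditions over the site that is then treated ten times with one of them. A participant who can tell the two apart has a reference for judging the treatment.

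The operator is a second route. Sham trains need a sham coil, and the only one described is a coded treatment coil. Someone who selects it knowingly has the code for that stimulator. Someone who uses A and B without knowing the key can still compare how the two letters affect tapping.

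FM-UE and ARAT performance depends partly on effort, and the Stroke Impact Scale and EQ-5D-5L are self-reported, so expectation could enter the active-sham difference at this centre. The primary model would not remove it: a random centre effect absorbs differences in level between centres, not a bias in the treatment contrast within one.

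**Working it through.** **1. The passages side by side**

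| Feature | Disruption test (protocol 8.3) | cTBS course (protocol 5.1, 8.2) |
|---|---|---|
| Target | Contralesional M1 | Contralesional M1 |
| Conditions per participant | Active and sham | Active or sham |
| Stimulus | 10 Hz, 90% RMT, 30 pulses over 3 s | 50 Hz triplets at 5 per second, 70% RMT, 40 s |
| Coil | Not stated | Coded A or B |
| Operator and masking | Not stated | Therapist and patient masked |

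The health-economic plan, section 4.2, explains that a separate threshold coil and neuronavigation are used so that therapist and patient stay masked to the treatment coil. The disruption test has no comparable protection.

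**2. Use of the test.** It has a row in protocol Table 1 but none in SAP Table 1. It is in neither list of objectives (protocol section 2, SAP section 1), and neither protocol section 10 nor SAP sections 7.4 to 7.7 analyses it. Protocol section 8.3 collects the patient's guess of treatment, but the SAP does not analyse that either.

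**3. The plan's own sample size.** Inputs from protocol section 4.4: difference 6.6, SD 23, two-sided alpha 0.05, power 0.85.

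n per arm = 2 × 23² × (1.960 + 1.036)² / 6.6² ≈ 218.1, so 219 per arm and 438 in total. The exact t-test needs 219.03, so 220 per arm and 440 in total, as stated. The masking question does not change this figure.

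**4. Possible size of the bias.** The documents give neither De Hoogstraat's share of recruitment nor any unmasking effect, so both are assumed here.

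- Exposed under equal accrual: 454 / 16 = 28.4, about 28. This is an upper limit at that share, because the test is optional.
- Shift in the overall contrast = share × bias among those exposed.
- Standard error = 23 × √(2/220) = 2.19.
- Type I error = P(|Z + shift/SE| > 1.96).

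Example: 0.25 × 6.6 = 1.65; 1.65 / 2.19 = 0.75; type I error = 0.117.

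Each cell gives the shift in FM-UE points, with type I error in brackets:

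| Share (participants) | Bias 2 | Bias 3.3 | Bias 6.6 |
|---|---|---|---|
| 1/16 (28) | 0.125 (0.050) | 0.21 (0.051) | 0.41 (0.054) |
| 25% (114) | 0.50 (0.056) | 0.82 (0.066) | 1.65 (0.117) |
| 40% (182) | 0.80 (0.065) | 1.32 (0.092) | 2.64 (0.226) |

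With a bias of 1 point at a 1/16 share the shift is 0.06. The standard error is the unadjusted one behind the sample size. If baseline adjustment reduces it, type I error for a given shift is somewhat higher.

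**5. Cost of excluding participants.** Leaving out the whole centre is the extreme case. Of 440, it leaves 412.5 at a 1/16 share (power about 83%) and 330 at 25% (about 74%).

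**The case against.** The strongest reply is that the text shows an opportunity for unmasking, not unmasking itself. Much of this stands.

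- **The stimuli differ.** A short 10 Hz train at 90% RMT during maximal tapping is not 40 s of theta bursts at 70% RMT. Participants at every centre also feel real TMS during threshold determination. What the test adds is a sham reference, and whether that tells anyone their allocation is unknown.
- **The coil is not stated.** A reader might infer that the sham trains must use coil A or B. Section 6.1 describes the equipment for cTBS, and nothing rules out another coil for the test. Even with the coded coils, an operator would learn the letters only if the effect on tapping were visible and consistent, and section 8.1.2 treats that effect as an open question.
- **Wider consequences are not documented.** A reader might infer that the trains are given back to back, that a leak would reach other centres, or that therapists would treat the arms differently. Order and spacing are not given, the documents do not say that A means the same condition everywhere, and the test's operator is not named.
- **The active pulses are not a bias between arms.** The test gives 5 × 30 = 150 active pulses, but it precedes treatment and is not tied to allocation, so both arms receive them alike. They are 2.5% of the 10 × 600 = 6,000 pulses of an active course.
- **The test has a stated purpose.** It may predict treatment outcome, so an analysis could be added instead of removing the test.

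What remains is that the protocol gives both conditions to the same participant before a masked course, leaves coil and operator open, and states no safeguard.

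**Conclusion.** The concern holds as a risk to masking at one centre. It is established that the optional test exposes a participant to both active and sham stimulation over the later treatment target, that no safeguard is described, and that no objective or planned analysis needs the test. Risk to the operator's masking is conditional on use of the coded coils.

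The documents do not support the stronger reading that the trial's masking is broken or the primary comparison invalid. At a 1/16 share, even a bias of 6.6 points among all exposed participants moves the contrast by 0.41 points and type I error to 0.054. A shift above 1 point needs a large share and a large bias together, such as 25% with 6.6 points or 40% with 3.3. Shares and biases are assumptions throughout.

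The change is still worth making, because it is cheap and the current plan could neither prevent nor reveal such a bias.

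**What to change.** 1. **Protocol section 8.3** (with 8.1.2 and Table 1): for randomised participants, drop the disruption test. Otherwise, state that the coded treatment coils are never used for it, and that its operator does not deliver that participant's cTBS, upper limb therapy or outcome assessments.
2. **Case report form:** record who had the test.
3. **SAP section 7.6:** add a sensitivity analysis that fits the primary model without exposed participants. If testing is decided without knowledge of allocation, the remaining comparison stays randomised. This analysis does not cover untested participants treated by someone who has learned the code, so item 1 is still needed.
4. **SAP:** tabulate the treatment guess already collected, by arm and by exposure.

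The cost is one amendment, one data item, one table and one further model fit. The sample size is unchanged. The downside is possible loss of an exploratory single-centre predictor, and lower precision in the sensitivity analysis: slight at a 1/16 share, more if the centre recruits a large share. Changing the coil keys at other centres mid-trial is not recommended, since relabelling carries its own risk of error and unmasking.
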